### Participant timeline {13}

Participant’s timeline is reported in Fig. 1.

**Fig. 1 Fig1:**
[figure not shown]
Participants’ timeline. *In mechanically ventilated patients. **In women of childbearing age. ***On days 1 and 2

### Sample size {14}

The sample size was computed through data simulations based on the following hypotheses:
Ninety-day mortality 45% in the control group, and 40% in the intervention group (i.e., relative reduction 11%)Mean ± standard deviation (*SD*) VFD at day 60 28 ± 16.5 in the control group and 34.5 ± 13 in the intervention group

The expected mortality in patients with COVID-19 and moderate to severe ARDS is between 34 and 50% [1]. The mean and *SD* of VFD at day 60 in the control group was taken from the subgroup of patients with PaO_2_/FiO_2_ < 150 mmHg included in the control group of the prospective randomized Xtravent-study comparing ultra-protective ventilation with extracorporeal CO_2_ removal versus conventional protective ventilation [7]. To be conservative, we have chosen to take an expected difference between the two groups of the present study corresponding to 50% of the difference observed in the Xtravent-study between the control and the intervention groups.

For each scenario corresponding to a given sample size, 1000 datasets were simulated. For each simulation, the score was computed for each patient and compared between the two groups using the test of Mann and Whitney. The power was computed as the proportion of tests with a bilateral *p*-value < 0.05.

The results of the simulations allowed us to determine that the inclusion of 100 patients per group will achieve a power greater than 80% to conclude a significant difference between the groups.

The simulations were implemented by two biostatisticians with the SAS software, version 9.4 (Copyright (c) 2002–2003 by SAS Institute Inc., Cary, NC, USA) and the R software, version 3.6.1 (R Core Team (2012)). The results were similar.

To account for premature exits from the study (withdrawal of informed consent for example), we have planned to add 10% more patients (10 supplementary patients in each group for a total of 220 patients).

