### Outcomes {12}

#### Primary outcome

The primary outcome is a composite score based on 90-day all-cause mortality as the first criterion and the number of VFD at day 60 after inclusion as the second criterion. The composite score will be obtained by comparing each patient of one group to all patients of the other group. For each pair, a value of + 1 (favorable), − 1 (unfavorable), or 0 (neutral) will be given to each patient. The score will be built as follows:
A value of + 1 will be given for a patient alive at day 90 paired with a patient deceased at day 90.A value of + 1 will be given for a patient alive at day 90 paired with a patient alive at day 90 but with a lower number of VFD.A value of 0 will be given for pairs with both patients deceased at day 90.A value of 0 will be given in case of an identical number of VFD for the pairs of patients alive at day 90.A value of − 1 will be given for a deceased patient in comparison with patients alive at day 90.A value of − 1 will be given for a patient alive at day 90 paired with a patient alive at day 90 but with a higher number of VFD.

For a given patient, the score will correspond to the sum of values resulting in the comparison to all patients of the other group.

VFD will be computed as follows from the day of inclusion:
VFD = 0 if the patient dies between inclusion and day 60VFD = 60 − *x* if the patient is successfully weaned from invasive mechanical ventilation, with *x* being the number of days from inclusion to last successful extubation. Successful weaning from mechanical ventilation will be defined as extubation without reintubation within at least 48 h (or weaning from mechanical ventilation for at least 48 h for patients with tracheostomy)VFD = 0 if the patient is mechanically ventilated for more than 60 days after inclusion

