#### Analysis of the primary outcome

The main analysis will be carried out by intention to treat, i.e., all the patients included in the study will be analyzed in their initial randomization group regardless of whether the allocated ventilation strategy was effectively applied or not.

The distribution of the composite score will be described in each group using the following statistics: mean, standard deviation, quartiles, and minimum and maximum values. It will be compared between the two groups using the test of Mann and Whitney.

The ULTV effect size will be quantified by the probability of a favorable result for a patient belonging to the ULTV arm in comparison with a patient belonging to the protective ventilation arm. This probability will be estimated by the proportion of pairs for which the patient of the ULTV arm will have a favorable result [20]. This estimate will be given with a 95% confidence interval.

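### The stated power above 80% with 100 patients per group comes from an invalid test of the composite score; on the protocol's own assumptions a valid test has about 38% power

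*Protocol article*

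**What the plan says.** The section Sample size {14} of the protocol article gives the inputs, the procedure and the result.

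- **Inputs.** 90-day mortality is 45% in the control group and 40% in the intervention group. VFD at day 60 (mean ± SD) is "28 ± 16.5 in the control group and 34.5 ± 13 in the intervention group". The VFD difference was set at half of that seen in an earlier trial.
- **Procedure.** In each of 1000 simulated datasets per scenario, "the score was computed for each patient and compared between the two groups using the test of Mann and Whitney". Power was the share of tests with a two-sided p-value below 0.05.
- **Result.** "the inclusion of 100 patients per group will achieve a power greater than 80% to conclude a significant difference between the groups". Ten patients per group are then added for early exits, giving 220 in all.

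The score is defined under Primary outcome: "The composite score will be obtained by comparing each patient of one group to all patients of the other group". Each pair gives +1, 0 or −1, and for one patient "the score will correspond to the sum of values resulting in the comparison to all patients of the other group". The section Analysis of the primary outcome plans the same test on the same score: "It will be compared between the two groups using the test of Mann and Whitney". No type I error of this procedure is reported.

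**The concern.** Mann-Whitney assumes two independent samples. These scores are not independent, because each arm's scores are built from the other arm's outcomes. With equal arms the two mean scores are exact mirror images, so any chance imbalance moves one arm up and the other down.

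The deaths show this most clearly. Take the expected counts: 60 survivors and 40 deaths on ultra-low tidal volume ventilation (ULTV), 55 survivors and 45 deaths on control. Every dead ULTV patient scores −55 (beaten by 55 control survivors) and every dead control patient scores −60. The 40 × 45 = 1800 pairs of deaths, defined as ties, all become wins for ULTV once the scores are ranked. A survival difference of a single patient, arising by chance, would do the same.

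A rejection rate from such a test cannot be read as power. If the real power is far lower, the trial is presented as adequately sized when it is not. Once the test is corrected, a neutral result could be taken as evidence of no benefit when the planned benefit would usually have been missed.

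**Working it through.** **Inputs.** Mortality 0.45 and 0.40, VFD 28 ± 16.5 and 34.5 ± 13, two-sided 0.05 and 100 per group, all from Sample size {14}. The score comes from Primary outcome.

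**Which patients the VFD figures describe.** If deaths counted as VFD = 0 within these means, the overall SD could not be below mean × √(p/(1−p)):
- control: 28 × √(0.45/0.55) = 25.3, against the stated 16.5
- intervention: 34.5 × √(0.40/0.60) = 28.2, against the stated 13

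The figures can therefore only describe survivors, and they are used that way below.

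**Step 1: reproduce the plan's figure.** Deaths were drawn at the stated rates and survivors' VFD from the stated means and SDs. Each patient was scored against the opposite arm and the scores compared by Mann-Whitney. At 100 per group the rejection rate is 81% to 82% for normal, clipped-and-rounded normal, truncated normal and beta shapes. This matches the article. About 5 to 6 of those percentage points are rejections in favour of control.

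**Step 2: the same procedure with no effect.**
- Both arms at the control values: rejects in about 88% of datasets.
- Both arms at the intervention values: rejects in about 78%.

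Doubling the VFD difference to 13 days leaves the rejection rate at about 79% to 80%. A rate that is about as high under no effect as under the planned effect, and does not rise when the effect is doubled, does not measure power.

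**Step 3: the effect implied by the assumptions.**
- P(ULTV survivor has more VFD than control survivor): q = Φ(6.5/√(16.5² + 13²)) = Φ(6.5/21.0) = 0.6215
- Win: 0.60 × 0.45 + 0.60 × 0.55 × q = 0.270 + 0.205 = 0.475
- Loss: 0.40 × 0.55 + 0.33 × (1 − q) = 0.220 + 0.125 = 0.345
- Tie (both dead): 0.40 × 0.45 = 0.18
- Win + half ties: 0.475 + 0.09 = 0.565

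**Step 4: power of a valid test.** The tie-corrected null standard error, with a pooled death rate of 0.425, is

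SE = √[(1/12)(2/100)(1 − 0.425³)] = √(0.01667 × 0.9232/10) = 0.0392

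Z = 0.065/0.0392 = 1.66, so power = Φ(1.66 − 1.96) = 0.38.

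**Step 5: check by simulation.** Mann-Whitney on the death-then-VFD ranking rejects in about 5% of null datasets.

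| Scenario | Power |
|---|---|
| 100 per group, Mann-Whitney on the ranking (20,000 datasets) | 38.1% |
| 100 per group, over VFD shapes | 35–39% |
| 100 per group, Finkelstein-Schoenfeld | 38.5% |
| 100 per group, net-benefit U-statistic | 38.6% |
| 100 per group, deaths confined to the lowest-VFD patients | 35% |
| 110 per group | 41–42% |
| 280 / 290 per group | 80% / 81% |
| 100 per group, full 13-day VFD difference | about 73% |

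**Step 6: what 100 per group can detect.** For 80% power, win + half ties must reach 0.5 + (1.96 + 0.84) × 0.0392 = 0.61, a win odds of 0.61/0.39 = 1.56. The planned value is 0.565, a win odds of 0.565/0.435 = 1.30.

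**The case against.** - **The figure is not a miscalculation.** It follows from the described simulation, and two biostatisticians obtained similar results in SAS and R. That is true, but it shows only that the same procedure was coded twice. It does not test the procedure's validity.
- **The 38% belongs to a test the protocol does not plan.** This stands as a clarification. With the analysis as now written, the first danger is false positives; low power becomes the problem once the test is corrected. Both have the same cause and must be fixed together.
- **Some assumptions are not stated in the article.** The 38% takes VFD to describe survivors and to be unrelated to the risk of death. The first is forced by the arithmetic. For the second, confining deaths to the lowest-VFD patients gives 35%.
- **Another valid analysis might reach 80%.** One-sided testing at 0.05 gives 51%, and Mann-Whitney in survivors only gives 61%. VFD alone, with 100 values per arm and mortality ignored, does exceed 80% (about 85%), but that is not the primary endpoint. The claim is therefore limited to valid tests of the composite.
- **The effect estimate will carry a 95% confidence interval.** This helps interpretation, but it does not support the power statement, and the article does not say that the interval governs how a non-significant result is read.
- **The full protocol versions are additional files that were not available here.** They may hold more detail, but the article states the score, the test and the result explicitly.

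**Conclusion.** The concern holds. The stated power above 80% is a property of an invalid test that rejects in 78% to 88% of trials with no effect. On the protocol's own inputs a valid test of the composite has about 38% power at 100 per group (35% to 39% over the variants tried) and 41% to 42% at 110, so the claim is overstated by more than 40 percentage points. With a valid analysis the trial would miss its planned effect about six times in ten. The exact figure depends modestly on the VFD shape and on how VFD relates to death, but no valid two-sided test of the composite came near 80%.

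**What to change.** 1. Re-run the simulation with a pooled-rank test: score every patient against all patients of both arms and use the Finkelstein-Schoenfeld variance, or equivalently apply Mann-Whitney to the death-then-VFD ranking. Report its type I error next to its power.
2. Restate the power in Sample size {14} as about 38% at 100 per group and 41% at 110, and the effect detectable with 80% power at 100 per group as a win odds of about 1.56.
3. Replace the test in Analysis of the primary outcome with the same valid one. Otherwise the restated power does not describe the analysis that will be done.
4. State in advance that a non-significant result will be interpreted from the confidence interval of the effect estimate, not as evidence of no benefit.

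The cost is re-running existing code and rewording two sections, with a less favourable figure. No extra patients are needed to correct the statement. That does not restore 80% power, which would take about 285 per group (570 in all, against the planned 220).

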### Recruitment {15}

SARS-COV-2 epidemic is currently active in France, with a massive afflux of patients in intensive care units. Most participating centers are almost exclusively dedicated to COVID-19 patients during the peak of epidemic waves, with extended capacities, which will ensure a high inclusion rate. At the time of study design, the anticipated duration of this epidemic was several weeks for the first wave, with expected consecutive waves. The study protocol of the intervention group was successfully tested in a pilot multicenter study in 11 academic and non-academic centers, emphasizing the feasibility of the study in the multicenter design [8].

To ensure an adequate number of participants will be enrolled in the required time frame, the participating centers will be asked to report on a regular basis their problems related to enrollment in order to find adequate responses to increase the enrollment rate. This led to the modification of the trial eligibility criteria regarding co-inclusions in trials testing unlicensed new drugs or medical devices (see above). Additional centers will be sought in case the enrollment rate in the trial is too low. Finally, a 1-year extension of the study time frame will be proposed in case the enrollment rate in the trial is too low.

## Assignment of interventions: allocation

### Sequence generation {16a}

The procedure proc plan of the SAS software will be used to generate a randomization list stratified by center, with a 1:1 ratio, using random blocks of sizes 4 and 6.

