### Study setting {9}

The study will be conducted in 11 intensive care units located in both academic and non-academic French hospitals (Additional file 4).

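### Randomisation is stratified by centre but the primary rank test is not: the test stays valid on ordinary outcome ranks, and a centre-stratified version would be a small, cheap gain if centres differ (minor).

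*Protocol article*

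**What the plan says.** - **Allocation.** The abstract and Sequence generation {16a} stratify by recruiting site; the latter says that a SAS procedure "will be used to generate a randomization list stratified by center, with a 1:1 ratio, using random blocks of sizes 4 and 6". Centre is the only stratification factor.
- **Centres.** Study setting {9}: "The study will be conducted in 11 intensive care units". They are a mix of academic and non-academic hospitals. With 200 to 220 patients that is 200/11 = 18 to 220/11 = 20 per centre on average.
- **Score.** Under Primary outcome, "the score will correspond to the sum of values resulting in the comparison to all patients of the other group", so patients are compared across centres as well as within them.
- **Test and effect measure.** Analysis of the primary outcome applies an unstratified Mann-Whitney test to the score. Of the probability of a favourable result it says: "This probability will be estimated by the proportion of pairs for which the patient of the ULTV arm will have a favorable result". A 95% confidence interval is planned. Neither the test nor the estimate has a centre term.
- **Power.** Sample size {14} simulates datasets defined by arm only, analyses them with the same unstratified test, and reports power above 80% with 100 patients per group.

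The article states this method outright. It is not a detail left open for an analysis plan.

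**The concern.** An analysis normally reflects the restrictions placed on the randomisation. Blocking within centre keeps the arms nearly balanced in each centre, so differences between centres largely cancel from the comparison of arms. The unstratified Mann-Whitney variance assumes unrestricted allocation and still counts those differences as noise. If centres differ in mortality or in time to extubation, the standard error is then too large for the design used, and some power is lost.

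Most pairs in the score are cross-centre: with 11 equal centres about 10/11 = 91%. Recruitment {15} and the Discussion describe worries about enrolment and limited funding, so precision that needs no extra patients is worth having. What is at stake is efficiency and agreement between design and analysis. Bias is not in question.

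**Working it through.** **Inputs from the article.** 11 centres; 1:1 allocation in blocks of 4 and 6 within centre; 100 per group; two-sided 5% level. Mortality: "Ninety-day mortality 45% in the control group, and 40% in the intervention group". Ventilator-free days (mean ± SD): "28 ± 16.5 in the control group and 34.5 ± 13 in the intervention group".

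**Assumed, because the article does not give it.** Between-centre SD of 0 to 0.7 on the logit scale; unequal centre sizes; ventilator-free days normal in survivors, rounded and limited to 0 to 60; deaths ranked lowest. The latent intraclass correlation is SD²/(SD² + π²/3). This is 0.25/3.54 = 0.07 at SD 0.5 and 0.49/3.78 = 0.13 at SD 0.7.

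**1. The plan's own power.** Scoring each patient against the other arm only, and then applying Mann-Whitney to those scores, gives 80 to 82% power at 100 per group. That matches the stated figure. The same procedure rejects in about 88% of datasets with no difference between arms. An ordinary Mann-Whitney test on the ordered outcome holds its level and gives about 39%. The comparisons below use this ordinary test as the baseline.

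**2. The tests.** Let r be the rank among all N patients, n1 and n0 the arm sizes, and k the centre.

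- Unstratified: numerator Σ(r, ULTV) − n1(N+1)/2; variance n1·n0/[N(N−1)] × Σ(r − r̄)².
- Centre-stratified on pooled ranks: numerator Σk[Σ(r, ULTV in k) − n1k·r̄k]; variance Σk n1k·n0k/[nk(nk−1)] × Σ(r − r̄k)².
- Van Elteren: as the second, but with ranks formed within each centre and each centre weighted by 1/(nk+1).

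The first variance contains the between-centre sum of squares; the second does not.

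**3. Hand check of conservatism.** If centre explains a share ρ of the rank variance and allocation is balanced within centre, the unstratified statistic has null SD of about √(1−ρ), and the type I error is 2Φ(−1.96/√(1−ρ)).

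- ρ = 0.05: 1.96/0.975 = 2.01, giving 4.4%.
- ρ = 0.10: 1.96/0.949 = 2.07, giving 3.9%.

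Simulation with latent correlations of 0.05 and 0.10 gave 4.5% and 3.7%.

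**4. Simulated power, N = 200, 11 unequal centres, centre acting on both mortality and ventilator-free days.**

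| Centre SD (logit) | Unstratified | Van Elteren | Difference (points) |
|---|---|---|---|
| 0 | 39.2% | 37.5% | −1.7 |
| 0.35 | 37.6% | 37.6% | 0.0 |
| 0.5 | 35.4% | 37.4% | +2.0 |
| 0.7 | 33.6% | 37.9% | +4.3 |

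Unstratified type I error was about 4% at SD 0.5 and 3.7% at SD 0.7. The centre-stratified test on pooled ranks lost about 0.5 point at SD 0 and gained about 1 to 5 points at the other values.

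**5. Further runs.**

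- Centre sizes 40, 32, 28, 24, 20, 16, 14, 10, 8, 4, 4 (2,000 datasets, Monte Carlo error about 1 point). Unstratified against van Elteren: 37.9% and 36.8% at SD 0; 36.4% and 36.4% at SD 0.35; 34.6% and 36.2% at SD 0.5; 33.7% and 37.2% at SD 0.7.
- Another set of unequal sizes, indexed by latent correlation: 37.7% and 36.3% at 0; 37.1% and 36.8% at 0.02; 36.7% and 37.3% at 0.05; 35.6% and 38.3% at 0.10.

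Across all runs the van Elteren loss with identical centres is 1.1 to 1.7 points, and the gain at SD 0.7 is 3.5 to 4.3 points.

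**The case against.** **The gain may be nil.** Below a centre SD of about 0.35 van Elteren gains nothing and can lose a little. The article also standardises ventilation and weaning in both arms, which should reduce centre differences, and it allows centres to be added, which would create more small strata. This stands. It is why the size is given as a range around zero and why the pooled-rank version is preferred.

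**The planned test is valid.** A reader might infer that ignoring the stratification invalidates the primary test. On ordinary outcome ranks it does not: type I error is at or slightly below 5%. Equally, a reader should not take the procedure as literally written to be conservative. Mann-Whitney on scores formed against the other arm only is strongly anti-conservative (step 1). That is a separate and much larger problem, which stratifying by centre does not address.

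**Baseline severity.** A reader might go on to infer that leaving age, SAPS2, SOFA and oxygenation out of the primary test is also an error with a larger loss. The article does not support this. Severity was not a stratification factor, so nothing is contradicted. An unadjusted primary test is a legitimate choice, and a supportive adjusted analysis is commonly left to the analysis plan. The only prognostic figure given, 34% against 50% mortality in moderate and severe ARDS, corresponds to about 4% of latent variance at an assumed equal mix. Larger gains need a prognostic strength that the article does not state.

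**Within-centre pairs would redefine the outcome.** The score and effect size are defined over all pairs. This stands against a purely within-centre win measure. It does not count against ranking all patients together and changing only the test variance.

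**Conclusion.** The mismatch is real and stands in the text: centre is used to allocate but appears in neither the primary test nor the power simulation. On ordinary outcome ranks the consequence is slight conservatism when centres differ materially (type I error about 3.7 to 4% at an assumed SD of 0.5 to 0.7) and a small amount of power forgone. Over assumed SDs of 0 to 0.7 the change in power is about -1.5 to +4 points for van Elteren and about -0.5 to +5 points for the pooled-rank version.

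Confidence in the mismatch is high. Confidence in the size is limited, because it depends on a centre effect and on centre sizes that the article does not give. Severity is minor. The change would leave power on a valid test near 38%, so it does not repair the gap to the stated figure of more than 80%.

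**What to change.** In Analysis of the primary outcome:

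1. Make the primary comparison a centre-stratified rank test. Preferably rank all patients together and take the test variance within centre (second form in step 2 of the working).
2. State in advance, without reference to outcomes by arm, how very small centres are pooled.
3. Keep the all-pairs proportion of favourable results as the effect measure, with its confidence interval on a variance that also respects centre, so that test and interval agree.
4. Retain the unstratified test as a sensitivity analysis. A severity-adjusted analysis is optional support only.

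The cost is a wording change and a pooling rule, plus about 0.5 point of power with pooled ranks (about 1.5 with van Elteren) if centres are identical. Enrolment began in April 2020, so this changes the primary analysis of a running trial. It should be dated and justified before outcomes are compared by arm.
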